### Plans to give access to the full protocol, participant-level data, and statistical code {31c}

Anonymized participant data may be shared from the corresponding author on reasonable request. There are no intentions to grant public access to participant data and statistical code.

## Oversight and monitoring

### Composition of the coordinating center and trial steering committee {5d}

The clinical monitoring activities will be performed by a day-to-day management group consisting of the principal investigator (PI), a doctoral student, a research coordinator, and an assistant manager. The group will meet weekly. This trial does not have a trial steering committee.

### Composition of the data monitoring committee, its role and reporting structure {21a}

No formal data monitoring committee has been established for this trial, as there are no interim analyses and no planned procedures for early stopping.

### Adverse events reporting and harms {22}

All adverse events, which refer to any negative or undesired reaction to the intervention, will be recorded through the patient-reported symptoms and observations by the researcher at each visit. Lung injury and hemorrhage, possibly caused by the US, have been reported in the past with acoustic pressure levels of at least 1 MPa, much higher than the LIPUS parameters proposed here. And to date, no adverse events have been reported with the low-power LIPUS regimen in soft tissue. Potential mild adverse reactions such as mild local swelling, spotting bleeding, enhanced local pain response, and local hyperesthesia or decrease. In case of corresponding symptoms, appropriate symptomatic treatment shall be carried out.

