### Criteria for discontinuing or modifying allocated interventions {11b}

Patients are free to withdraw from participation in the study at any time upon request, without any consequence. If a participant chooses to discontinue the study intervention, we will not collect or use their data.

LIPUS is an FDA-approved and safe treatment modality. To date, no adverse events have been reported with the low-power LIPUS regimen in soft tissue. Therefore, we anticipate that the risk to the safety of participants will be minimal. However, nursing staff will still monitor potential mild adverse reactions such as mild local swelling, spotting bleeding, enhanced local pain response, and local hyperesthesia or decrease. In case of corresponding symptoms, appropriate symptomatic treatment shall be carried out. Regardless, participants can withdraw from the study at any time if they experience adverse events that are unacceptable to them.

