### Plans to promote participant retention and complete follow-up {18b}

The patients will complete all evaluations and treatments during hospitalization. Lung CT examinations, ultrasound examinations, and trial-related laboratory examinations received by patients before and after treatment are provided free of charge. Once a patient withdraws from the study during treatment (does not complete the full 7-day treatment period), their data will not be retained. Every effort should be made to encourage patients to remain in the study for the duration of their planned outcome assessments.

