### Data management {19}

Investigators will collect data on participants’ baseline status and daily after randomization. All data obtained will be stored electronically in a securely accessible database and kept strictly confidential. The data transfer process will encrypt and any personally identifiable information will be deleted. De-identification of the data for analysis was allowed only during the final phase of this trial.

Registered participants will be withdrawn from the study if (1) the participant withdraws his/her consent and (2) the exclusion criteria is discovered after registration. The date and reason of the suspension will be recorded, and their data will not be retained.

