## Statistical methods

### Statistical methods for primary and secondary outcomes {20a}

Analysis of baseline characteristics of the three groups will be summarized by appropriate descriptive statistics. Analysis of both the primary and secondary outcomes will be performed blinded to treatment assignment and analyzed on the intention-to-treat approach [22], with all randomized participants retaining their original randomization group. If these missing data are judged to be random, multiple imputations of the chained equation will be used to address missing data caused by lost access and non-response.

Normally distributed data were expressed as the mean (standard deviation), whereas data not normally distributed was expressed as the median (interquartile range). The independent sample test was used for the comparison between groups, and the paired sample test was used for the comparison within the group before and after treatment. For clinical symptoms, variables were expressed as percentages. A *χ*^2^ test or Fisher’s exact test was used to compare categorical data. The conventional level of 0.05 for statistical significance was adopted to evaluate the *p*-values. Statistical analysis was carried out by using SPSS software, version 26.

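### Adverse events that lead a participant to stop can drop out of the harms record, although the protocol promises to record all of them

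*Protocol article*

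**What the plan says.** All references are to the protocol article.

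- **Adverse events reporting and harms {22}:** "All adverse events, which refer to any negative or undesired reaction to the intervention, will be recorded". The means of capture is that events are "recorded through the patient-reported symptoms and observations by the researcher at each visit".
- **Criteria for discontinuing or modifying allocated interventions {11b}:** "participants can withdraw from the study at any time if they experience adverse events that are unacceptable to them". The same section states: "If a participant chooses to discontinue the study intervention, we will not collect or use their data".
- **Plans to promote participant retention and complete follow-up {18b}:** for a patient who withdraws during treatment, the text reads "does not complete the full 7-day treatment period), their data will not be retained".
- **Data management {19}:** for participants withdrawn because consent is withdrawn or an exclusion criterion is found after registration, "The date and reason of the suspension will be recorded, and their data will not be retained".
- **Provisions for post-trial care {30}:** any injury due to taking part is evaluated, documented and cared for, with no exception for those who have left.
- **Statistical methods for primary and secondary outcomes {20a}:** outcomes are "analyzed on the intention-to-treat approach [22], with all randomized participants retaining their original randomization group".

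The Strengths and limitations section describes the study as, to the authors' knowledge, the first clinical study of the efficacy of therapeutic LIPUS in viral pneumonia.

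**The concern.** An unacceptable adverse event is the one reason for leaving that {11b} names, and leaving is what triggers loss of the data. In {11b} the trigger is stopping the intervention, not withdrawing consent, so respect for consent does not explain the rule. No section makes an exception for safety data.

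At stake is what the trial can say about harm. An event tolerable enough to let treatment continue stays in the record, while one that makes a participant stop can vanish from the event count and from the number at risk. The loss cannot be repaired once the trial is over, because the data will not exist.

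The definition of an adverse event adds a smaller problem. If an event must be a reaction to the device before it counts, someone has to judge cause before the arms are compared. Respiratory worsening put down to the pneumonia need not be recorded in any arm. A null-stimulus control allows such events to be compared without that prior judgement.

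**Working it through.** **Step 1: follow one participant through the text.** Suppose a participant starts sessions, has an event, finds it unacceptable and stops before day 7.

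| Section | Consequence |
|---|---|
| {22} | The event is recorded |
| {11b} | Data neither collected nor used |
| {18b} | Data not retained, as 7 days were not completed |
| {19} | If consent is withdrawn: date and reason kept, data not retained |
| {30} | If the event is an injury due to participation: documented |
| {20a} | Participant analysed in the randomized group |

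These cannot all be followed. The item kept under {19} is a date and a reason, not severity, course or outcome, and it is written for consent withdrawal and late-found exclusions. {11b} has no such provision for someone who only stops the intervention. Neither {19} nor {30} says that what is kept enters the harms report.

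**Step 2: number exposed.** Sample size {14} gives 66 participants at 1:1:1 and 70 after about 5% dropout. The inflation reproduces: 66/0.95 = 69.5, rounded up to 70. The 66 cannot be re-derived, since no effect size or SD is given, but this point does not depend on it. LIPUS is given in the intervention arm and the self-control arm: 66/3 = 22 per arm, 2 × 22 = 44 exposed.

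**Step 3: illustration with an assumed count.** Assume 2 of 44 have an event and stop. Exact (Clopper-Pearson) intervals:

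- All kept: 2/44 = 4.5%, 95% CI 0.6 to 15.5%.
- Those two removed: 0/42, upper limit 1 − 0.025^(1/42) = 8.4%.

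Other bases give much the same. With the abstract's 60 participants, 40 are exposed: 2/40 = 5.0% becomes 0/38, upper limit 1 − 0.025^(1/38) = 9.3%. With 70 randomized, 46 or 47 are exposed; taking 46, 2/46 = 4.3% becomes 0/44, upper limit 1 − 0.025^(1/44) = 8.0%.

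**Step 4: expected effect over a range.** Let q be the true risk of an event and s the share of affected participants who stop and are removed, with nobody else stopping. The rate seen among those retained is q(1 − s)/(1 − qs). The chance that at least one event is seen among n = 44 is 1 − (1 − q(1 − s))^44. Both q and s are assumptions.

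| q | s | Rate seen | Chance of seeing at least one |
|---|---|---|---|
| 10% | 0 | 10% | 0.99 |
| 10% | 0.5 | 0.05/0.95 = 5.3% | 0.895 |
| 10% | 1 | 0% | 0 |
| 5% | 0 | 5% | 0.895 |
| 5% | 0.5 | 0.025/0.975 = 2.6% | 0.67 |
| 5% | 1 | 0% | 0 |

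Removal can only lower the number of events. It lowers the rate as well whenever participants with an event stop more often than those without, which is what {11b} anticipates.

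**The case against.** The best defence is that the record is not wiped clean. {19} keeps the date and reason of withdrawal, {30} documents injuries due to participation, and a management group meets weekly ({5d}). That stands: a reader might infer that every trace of such an event is erased and the trial is bound to report none, and the text does not support this. But these provisions keep a note or trigger care. They do not put the event into a comparison of harms by arm.

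Four other strong readings are tempting and also fail.

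- **That the known lung hazard is ignored.** {22} does state "Lung injury and hemorrhage, possibly caused by the US, have been reported in the past", but it places those reports at acoustic pressures of at least 1 MPa, which it calls much higher than the parameters proposed. The local reactions it lists are examples, not a closed list.
- **That the day-7 CT is read for target-area inflammation and nothing else.** The Primary outcome section describes how efficacy is measured; it does not bar other findings. Daily oxygen saturation, daily auscultation, lung ultrasound, blood gases and sputum observations could also show lung harm.
- **That the definition defeats the null-stimulus control.** {17a} blinds patients, caregivers and outcome assessors. A narrow definition applied by blinded staff falls on the arms alike; it costs sensitivity but does not remove the comparison. {22} does not say whether the observing researcher is among the blinded.
- **That this is the first use of LIPUS on the lung.** The article claims only the first clinical study in viral pneumonia.

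The numbers are also fairly criticised. The count of 2 is assumed, 44 is taken before dropout inflation, and the upper limit of 8.4% still covers 4.5%. They show direction and scale, not a prediction.

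**Conclusion.** The contradiction is in the text and needs no assumption: {11b}, {18b} and {19} cannot be reconciled with {22} or with {20a}. As written, adverse events that lead to stopping can leave both numerator and denominator, so harms would be under-reported. Under the assumption of 2 such events among 44 exposed, an observed 4.5% with an upper limit of 15.5% would be presented as none, with an upper limit of 8.4%. The true size depends on event risk and stopping share, neither of which the article gives.

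A reader might infer that the most serious events are the ones lost. The text supports only that events leading to stopping can be lost. The attribution wording in the definition is a secondary weakness. The retention rule should be corrected before the data are affected, because what is not kept cannot be recovered.

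**What to change.** 1. Reconcile {11b}, {18b} and {19} with {20a} and {22}. State that, within the limits of consent, adverse-event data are kept for every randomized participant who started active or null sessions, including those who stop or withdraw, and are reported by arm.
2. Tabulate withdrawals for adverse events by arm, using the date and reason that {19} already keeps and extending that record to anyone who stops the intervention.
3. Define an adverse event as any untoward medical event after the first session regardless of cause, with relatedness recorded separately by blinded staff.

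The cost is changed wording in the protocol and case-report form and a few more recorded events. No new visit or examination is needed, and no treatment rule changes.

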## Outcomes {12}

### Primary outcome

The primary outcome measure will be the difference in the extent of absorption and dissipation of lung inflammation on CT images. Result comparisons will be made between the test group and the control group and between the LIPUS-treated and non-treated areas within the self-control group.

Pulmonary inflammation on CT images will be assessed by an expert chest radiologist before and 7 days after treatment to compare the area and volume of inflammation in the target area of the lung, as well as the area absorption rate (AAR) or volume absorption rate (VAR). A Pair software will be used to mark and 3D reconstruct the target area of CT images and record the data of pulmonary inflammation changes. AAR is defined as [(target site inflammation area before treatment − target site inflammation area after treatment)/target site inflammation area before treatment] × 100 (%). VAR is defined as [(target site inflammation volume before treatment − target site inflammation volume after treatment)/target site inflammation volume before treatment] × 100 (%).

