#### The sputum excretion volume

For patients who can cough spontaneously, nurses will collect and record the amount of sputum that can be excreted in 24 h, and those with negative pressure suction will use a disposable sputum suction device to record the amount of sputum excreted after each treatment. Collection by trained nurses takes place daily at 8:00 am and ends at 8:00 am the next day. Less than 10 ml/24 h is a small amount of sputum, 10–150 ml/24 h is a moderate amount of sputum, and more than 150 ml/24 h is a large amount of sputum. The color and consistency of the sputum will also be recorded.

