To date, no adverse events have been reported during LIPUS treatment. However, the exact biological effects of LIPUS in tissues are not fully understood. Although LIPUS has been investigated in many therapeutic applications experimentally or clinically and achieved good curative effects [29–31], further research is still needed to fully understand the exact mechanism in humans.

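### Lung injury and hemorrhage are named as reported ultrasound harms, but nothing in the plan routes the scheduled lung findings into adverse-event recording, so a silent lesion may go unrecorded

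*Protocol article*

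**What the plan says.** The section on adverse events and harms {22} of the protocol article names one lung-specific hazard of ultrasound: "Lung injury and hemorrhage, possibly caused by the US, have been reported in the past with acoustic pressure levels of at least 1 MPa". It continues that this level is "much higher than the LIPUS parameters proposed here", and adds that low-power LIPUS has produced no reported adverse events in soft tissue. The section on discontinuing or modifying interventions {11b} gives the same soft-tissue reassurance and then says that "nursing staff will still monitor potential mild adverse reactions such as mild local swelling, spotting bleeding, enhanced local pain response, and local hyperesthesia or decrease". The harms section repeats the list. In both places the items are offered as examples.

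All adverse events, defined as unwanted reactions to the intervention, "will be recorded through the patient-reported symptoms and observations by the researcher at each visit".

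The primary outcome comes from CT before and 7 days after treatment, read by an expert chest radiologist to "compare the area and volume of inflammation in the target area of the lung". The area and volume absorption rates (AAR, VAR) are the percentage falls in target-site inflammation. On sputum, the article says: "The color and consistency of the sputum will also be recorded". Lung ultrasound, fingertip oxygen saturation and auscultation are also scheduled. All of these appear under outcomes.

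**The concern.** The harms section identifies a hazard to the organ being treated, but the reactions staff are asked to watch for are all mild and local. The reasons for not looking further are weaker than they appear. The comparison with 1 MPa cannot be checked, because no acoustic pressure is given for the device and the trial status section says the stimulation parameters are still being confirmed. The clean record is confined to soft tissue, while the target here is inflamed lung, in what the authors believe is the first clinical study of this use.

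Capture is the practical problem. Symptoms and bedside observation are poor at finding a new lung opacity in someone who already has pneumonia. The investigations that could show one are scheduled as outcomes, with no stated route to the adverse-event record. Two things could follow. The trial could report a clean lung safety record without having searched for the named harm. And a lesion in the target area could be counted as inflammation that failed to clear, turning a harm into apparent lack of efficacy.

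**Working it through.** **1. Named harm against stated capture (Protocol article).**

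| Element | Section | Covers lung injury or hemorrhage? |
|---|---|---|
| Monitored reactions | {11b}, {22} | Not listed. The list is open, and its bleeding item sits among local reactions |
| General capture | {22} | All adverse events, but only through symptoms and observation |
| CT at baseline and day 7 | Primary outcome | Measures inflammation in the target area. No safety read and no rule for a new non-inflammatory opacity |
| Lung ultrasound, four regions per hemithorax | Lung ultrasound scoring system | Could show a change. No stated link to adverse events |
| Daily oxygen saturation and auscultation | Blood gas and SaO2; pulmonary rales | Could show a change. No stated link |
| Sputum color | Sputum excretion volume | Could show blood. No stated link |

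**2. Is the 1 MPa argument plausible?** The article states no pressure, so there is no plan figure to reproduce. It gives an intensity of 820 mW/cm² and a 50% duty cycle, without saying how the intensity is averaged. I used the plane-wave relation p = √(2·Z·I·r), with assumed impedance Z of 1.5 to 1.63 × 10⁶ rayl and an assumed spatial peak-to-average ratio r of 1 to 8.

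- 820 mW/cm² as a within-pulse value (8,200 W/m²), r = 1: √(2 × 1.5×10⁶ × 8,200) = 0.157 MPa. At the higher Z, 0.163 MPa.
- 820 mW/cm² as a time average, so 16,400 W/m² within the pulse, r = 1: 0.222 to 0.231 MPa.
- r = 8: 0.444 to 0.462 MPa (within-pulse) and 0.627 to 0.654 MPa (time average).

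Every case is below 1 MPa, by a factor of about 6.4 (1/0.157) down to about 1.5 (1/0.654). The article's argument is not contradicted, but how large the margin is depends on quantities it does not give.

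**3. What the endpoint definition permits.** VAR = (before − after)/before × 100. Assume 100 mL at baseline and 40 mL of true residual inflammation.

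- No new lesion: (100 − 40)/100 = 60%.
- New lesion of 10, 20 or 70 mL contoured as inflammation: (100 − 50)/100 = 50%, (100 − 60)/100 = 40%, (100 − 110)/100 = −10%.
- New lesion left out of the contour: VAR stays 60%, and the endpoint carries no trace of it.

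**4. What a clean search could show.** Two of three arms are sonicated. With the 66 participants of the sample size section, that is 44. With zero events the one-sided 95% upper bound is 1 − 0.05^(1/n): 6.6% for n = 44 and 12.7% for one arm of 22. These bounds apply only if lesions are looked for in everyone.

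**The case against.** The strongest reply is that this risk was considered, not overlooked: the harms section gives a reason for discounting it, and the rough pressures above agree with that reason. The monitoring list is open, all adverse events are to be recorded, and a lung bleed that someone notices is recordable as written. Patients are inpatients under daily auscultation and oxygen saturation checks, with lung ultrasound of both sides. The article condenses a fuller protocol, in which a reading manual or adverse-event procedures may deal with incidental CT findings.

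Most of this stands, and it limits the point. What remains is that the open list leaves out the one lung harm the authors name, that the reassurance cannot be checked from the article, and that none of the lung assessments is tied to safety recording.

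A reader might go further in three ways that the text does not support:

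- That the CT read would mis-score such a lesion. An expert chest radiologist may tell it from inflammation, and nothing requires every opacity to be contoured.
- That the lesion would not be seen. The non-treated area is also read in the self-control arm, and ultrasound, saturation, auscultation and sputum could each give a signal.
- That the Discussion's sentence "To date, no adverse events have been reported during LIPUS treatment" contradicts the harms section. It concerns LIPUS, whereas the harms section attributes lung injury to ultrasound at higher pressure.

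**Conclusion.** The point holds as a gap in safety capture. The article names lung injury and hemorrhage and discounts them on a comparison that cannot be verified from what it states. It then fixes a capture method under which a silent lung lesion may go unrecorded, and under which one inside the target area can, but need not, lower AAR or VAR. It does not show that the device reaches a harmful pressure or that such lesions are likely.

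No size can be estimated from the document. The fall in VAR from 60% to 40% rests on assumed volumes. The bounds of 6.6% and 12.7% follow from the sample size alone and would apply to any harm with zero events. Both are illustrations only. The pressure range rests on the assumed impedance and peak-to-average ratio. Procedures in a fuller protocol, not available here, could close part of the gap. The case for changing the text is that the improvement costs little in a study described as the first of its kind.

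**What to change.** - In sections {11b} and {22}, list lung injury and pulmonary hemorrhage as adverse events of special interest.
- At the existing baseline and day-7 CT reads, have the same blinded radiologist record any new suspected hemorrhage or injury opacity over the whole lung, and flag those participants for a sensitivity analysis of AAR and VAR.
- Record blood-stained sputum, taken from the existing sputum record, as an adverse event.
- Report counts by arm and by treated versus untreated area. The control arm then shows how often such findings occur without sonication.

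The cost is a few fields on the CT read and the sputum form, with no added scan, visit or reader. The downside is that CT cannot always separate hemorrhage from inflammation, so some flags will be uncertain. For that reason the flag feeds a sensitivity analysis and does not change the primary contour.
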